## Abstract

**Background:**

Live kidney donors (LKDs) account for nearly a third of kidney transplants in the United States. While donor nephrectomy poses minimal post-surgical risk, LKDs face an elevated adjusted risk of developing chronic diseases such as hypertension, diabetes, and end-stage renal disease. Routine screening presents an opportunity for the early detection and management of chronic conditions. Transplant hospital reporting requirements mandate the submission of laboratory and clinical data at 6-months, 1-year, and 2-years after kidney donation, but less than 50% of hospitals are able to comply. Strategies to increase patient engagement in follow-up efforts while minimizing administrative burden are needed. We seek to evaluate the effectiveness of using small financial incentives to promote patient compliance with LKD follow-up.

**Methods/design:**

We are conducting a two-arm randomized controlled trial (RCT) of patients who undergo live donor nephrectomy at The Johns Hopkins Hospital Comprehensive Transplant Center (MDJH) and the University of Maryland Medical Center Transplant Center (MDUM). Eligible donors will be recruited in-person at their first post-surgical clinic visit or over the phone. We will use block randomization to assign LKDs to the intervention ($25 gift card at each follow-up visit) or control arm (current standard of care). Follow-up compliance will be tracked over time. The primary outcome will be complete (all components addressed) and timely (60 days before or after expected visit date), submission of LKD follow-up data at required 6-month, 1-year, and 2-year time points. The secondary outcome will be transplant hospital-level compliance with federal reporting requirements at each visit. Rates will be compared between the two arms following the intention-to-treat principle.

**Discussion:**

Small financial incentivization might increase patient compliance in the context of LKD follow-up, without placing undue administrative burden on transplant providers. The findings of this RCT will inform potential center- and national-level initiatives to provide all LKDs with small financial incentives to promote engagement with post-donation monitoring efforts.

**Trial registration:**

ClinicalTrials.gov number: NCT03090646

Date of registration: March 2, 2017

Sponsors: Johns Hopkins University, University of Maryland Medical Center

Funding: The Living Legacy Foundation of Maryland

**Supplementary Information:**

The online version contains supplementary material available at 10.1186/s12882-020-02117-9.

## Background

Live donor kidney transplantation is the optimal treatment modality for patients with end-stage renal disease (ESRD), with superior clinical outcomes and quality of life compared to deceased donor kidney transplantation or remaining on dialysis [1–4]. Live kidney donors currently contribute nearly one third of the kidneys used for transplantation each year in the US [5].. While live kidney donation poses minimal post-surgical risks to patients [6–8], donors face a small but measurable increase in the risk of developing ESRD and other chronic diseases in the long-term [9–15]. Prior work suggests that donors who develop de novo disease are at greater risk for ESRD [16, 17]. Hypertension, diabetes mellitus, and glomerulonephritis account for over 60% of ESRD cases in donors [17]. Routine laboratory and clinical screening can detect subclinical disease indicators such as hyperglycemia, elevated blood pressure, proteinuria, and hematuria long before they progress to chronic disease or ESRD. In fact, our group’s preliminary work found that serum creatinine measured as early as 6 months postdonation was predictive of later ESRD development; a 10 mL/min/1.73m^2^ increase in postdonation eGFR was associated with 40% decreased risk of ESRD [18].

Transplant hospitals are required to monitor donors for 2 years postdonation but have historically struggled to meet federally-mandated data reporting requirements. For donors from 2008 to 2012, the vast majority of transplant hospitals had noncompliant 2-year follow-up data; 69 and 84% of hospitals were noncompliant with clinical and laboratory data reporting requirements, respectively [19]. In 2013, the Organ Procurement and Transplantation Network (OPTN) implemented a policy mandating that hospitals report clinical data (i.e. presence of hypertension, diabetes, dialysis, kidney related complications, recent hospitalizations, medical insurance status, income, and vital status) for 80% and laboratory data (i.e. serum creatinine and urine protein) for 75% of donors at 6-months, 1-year, and 2-years postdonation (Supplement 1). While the rate of compliant donor follow-up increased after this policy change (33% pre-policy to 54% post-policy), only 43% of transplant hospitals met all OPTN-mandated 6-month, 1-year, and 2-year thresholds for donors who donated in 2013 [20]. Transplant hospitals commonly cite barriers such as donor inconvenience, direct and indirect costs to donors, donors not wanting to return to the program, and the burden of data collection [21, 22]. Tools to improve donor engagement and strategies that mitigate patient and administrative burden are needed.

Financial incentives have been employed in many realms of healthcare to change health-related behaviors. Financial incentives include a variety of rewards that have an economic value for the recipient, including cash payments, coupons, goods, and services, and have been shown to positively influence both simple (i.e. accomplished through a single action) and complex (i.e. accomplished repeatedly over a period of time, often involving sustained lifestyle modifications) health-related behaviors [23]. Several randomized controlled trials (RCTs) and reviews have found financial incentivization to be associated with increased uptake of recommended preventive services, including smoking abstinence, vaccination, and preventive colonoscopy and mammogram screenings [23, 24]. For example, one RCT found that a $100 incentive more than doubled rates of employee participation in preventive colonoscopy screenings [25]. However, other RCTs have shown a benefit only in subgroups of patients who were at higher risk for poor adherence at baseline [26], while still others observed no difference in outcomes between a financial incentive intervention and control groups [23, 27]. Prior work suggests that the effectiveness of financial incentives in achieving health behavior often varies based on the characteristics of the population and health behavior of interest and may decrease over time [28–31]. Moreover, much of the published literature examining the use of financial incentivization to modify health behavior focuses on low-income populations [28].

Given that patient-level factors are commonly cited by transplant hospitals as barriers to compliance with federally-mandated donor follow-up thresholds [21, 22], financial incentives might be a valuable tool to promote patient engagement in postdonation monitoring efforts. However, given the uncertainty in the literature, an RCT is necessary to evaluate the effectiveness of using financial incentivization to promote patient compliance with follow-up care in this setting.

## Methods

### Objective

To evaluate the effectiveness of financial incentivization in increasing rates of compliance with postdonation follow-up among live kidney donors at two US transplant hospitals.

### Study design

This trial is designed as a randomized, controlled, nonblinded, two-arm, superiority trial with a 1:1 allocation ratio (NCT03090646). Patients who undergo donor nephrectomy at the Johns Hopkins Hospital Comprehensive Transplant Center (MDJH) and the University of Maryland Medical Center Transplant Center (MDUM) will be eligible for participation. The planned study recruitment period will be 4 years for MDJH and 3 years for MDUM. After consent and randomization, participants will be followed for the federally-mandated 2-year follow-up period (Fig. 1). The primary outcome will be the rate of policy-defined complete (all components addressed) and timely (within 60 days before or after the 6-month, 1-year, or 2-year postdonation date; i.e. 120-day period) submission of data at all 6-month, 1-year, and 2-year follow-up visits. The secondary outcome will be transplant hospital-level compliance with OPTN reporting requirements (submission of clinical data for 80% and laboratory data for 75% of donors) at each visit. Outcomes will be assessed separately for each follow-up time point and as a composite outcome over the study period, and will be compared between study arms following the intention-to-treat principle. We will also collect and report data related to potential logistical challenges of implementing the intervention (i.e., number of mailing attempts necessary, failed delivery attempts, incorrect or out-of-date contact information, etc.).

**Fig. 1 Fig1:**
[figure not shown]
Schematic of Study Design

#### Interventions

The Johns Hopkins Institutional Review Board (IRB) prefers using gift cards rather than cash compensation for clinical research. We chose to provide gift cards to Amazon.com because this online retailer is broadly accessible, and they have been used for other studies within our research group. The gift card will be mailed to participants assigned to the intervention arm after complete (i.e. all components addressed) and timely (i.e. within the 120-day period) submission of follow-up data at each 6-month, 1-year, and 2-year follow-up visit, for a total maximum financial incentive of $75. Each patient will have a 50% chance to be in the intervention arm of the study.

Per MDJH and MDUM policy, a follow-up visit can include either (1) attending an outpatient clinic visit at which the required clinical and laboratory data are collected or (2) submitting a questionnaire documenting a remote standard of care clinic visit and required laboratory values. Participants assigned to the intervention and control arms will receive the same care from the transplant hospital. In other words, those assigned to the control arm will be required to complete the same follow-up activities as those in the intervention arm (per standard of care), but will not receive a gift card. In the United States, donors receive no compensation for postdonation follow-up activities, so the intervention is the only financial incentive provided to donors.

### Study population

We will recruit donors for study participation at two urban US transplant programs affiliated with large, academic hospitals. Both MDJH and MDUM have an average annual volume of approximately 80 donors per year, and are considered large-volume transplant hospitals.

We plan to enroll 320 participants during the study period. Donors randomized to the intervention arm (approx. *N* = 160) will receive a gift card upon completion of each follow-up visit. Donors randomized to the control arm (approx. *N* = 160) will receive the standard of care for donor follow-up at MDJH and MDUM.

#### Inclusion and exclusion criteria

Donors who undergo nephrectomy at MDJH and MDUM in the study period will be eligible for participation in this RCT. We will exclude only donors who do not speak English, do not live in the US, or do not consent to participate in the study. Per national policy, all living donors are ≥18 years of age.

### Study procedures

Study personnel at each site will be responsible for approaching patients who undergo donor nephrectomy at their respective sites (i.e. MDJH study personnel will recruit MDJH patients and MDUM study personnel will recruit MDUM patients). At each site, study personnel will obtain a list of patients who have undergone donor nephrectomy from surgical providers (co-investigators on this study) or hospital records and will approach all of these patients as possible participants. Only requisite study personnel will have access to lists of potential patients. Study personnel will approach donors in one of the following settings: (1) the inpatient clinical transplant unit after patients have undergone donor nephrectomy, prior to their discharge; or (2) at the donor’s first medically-required outpatient clinic visit. Informed consent will be documented using a written consent form. If patients are unable to be contacted at these times, study personnel will contact the patient via telephone and describe the study using a telephone screening script. If patients are not interested in learning more about the study, study personnel will record this refusal. If patients are interested in participating, study personnel will use an oral consent script to obtain consent. The number of acceptances, eligible enrollments, and refusals will be recorded; then the list will be destroyed. Surgeon and clinician members of the study team will not participate in recruitment activities to avoid the potential for coercion and appearance of conflict of interest. As much time as necessary will be allowed for obtaining consent. After providing informed consent, participants will be randomized to the intervention or the control arms using opaque, sealed envelopes.

All study participants will be instructed to complete required follow-up activities as is standard of care. Study personnel at MDJH and MDUM will monitor patient compliance with 6-month, 1-year, and 2-year follow-up. Study personnel at MDUM will provide periodic enrollment and follow-up compliance updates to the MDJH study team using a HIPAA-compliant REDCap database [32]. Enrollment data will include patient name, date of birth, date of donation, demographic information (including gender, race, and ethnicity), contact information, and an electronic copy of the informed consent form. Follow-up compliance data will include the dates of completion of clinical (i.e. questionnaire) and laboratory follow-up components for each participant. Only requisite study personnel will have access to the REDCap database.

The MDJH study team will mail gift cards to participants enrolled at both MDJH and MDUM who were assigned to the intervention arm. Gift cards will be mailed with a letter reminding participants that the gift card is for their complete and timely submission of required donor follow-up activities. Gift cards will be mailed using USPS Domestic Certified Mail, which requires the recipient to sign for the letter at the time of delivery and provides the sender with a mailing receipt and electronic verification of delivery. The number of mailing attempts and dates of gift card mailing and receipt by the participant will be recorded.

There will not be study-specific efforts to retain participants, as this would be a form of intervention that might impact outcomes. However, transplant providers at MDJH or MDUM may contact donors for the purpose of obtaining complete and timely follow-up data in order to comply with nationally-mandated follow-up requirements. The hospital protocols for continued patient follow-up are consistent between MDJH and MDUM. Participants may withdraw from the RCT at any time without penalty. Withdrawal from the RCT would not preclude participants from obtaining regular medical care or follow-up care related to their kidney donation. If participants choose to withdraw, the study team will use the data collected prior to withdrawal and mark the remaining data as censored. Other than interventions that might impact rates of donor follow-up compliance, no concomitant care or interventions will be prohibited during the trial.

#### Data collection

The enrollment data for MDJH and MDUM will be added by site personnel to a HIPAA-compliant REDCap database. We will collect the name, birth date, donation date, demographic information (gender, race, ethnicity), and contact information for every patient who consents to participate. We will also collect follow-up compliance data, including the dates of completion of clinical (questionnaire) and laboratory follow-up components for each participant. For participants in the intervention arm, we also record the dates that each gift card was mailed and received, and if there was a failed delivery of the gift card via the USPS Certified Mail tracking system.

### Statistical analysis

Rates of patient and center-level compliance for each 6-month, 1-year, and 2-year follow-up visit will be compared between study arms using Fischer’s exact test. Rates of patient and center-level compliance for the composite outcome of compliant 6-month, 1-year, AND 2-year follow-up visit will be compared between study arms using Pearson’s chi-squared test. All analyses will follow an intent-to-treat principle. Data will be analyzed by data analysts on the MDJH study team using Stata 15/MP for Linux (College Station, Texas).

Our primary end-points are the living donor policy defined outcomes of complete and timely 6-month, 1-year, and 2-year follow-up. The motivation for these outcomes is to align our findings with the relevant policy end-points, not to maximize statistical power. As an additional secondary aim, generalized estimating equations (GEE) will be used to estimate population-averaged changes in complete and timely follow-up over the full course of the study. This approach will allow for participants with non-policy compliant follow-up behaviors (e.g. missing 1-year follow-up but completing 6- and 2-year follow-up) to be counted towards a population average. This may provide insight on alternative designs for the living donor follow-up policy.

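### The primary composite is tested without covariates, so any prognostic information in the baseline data already collected goes unused

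*Protocol article*

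**What the plan says.** The Study design section defines the primary outcome as the rate of complete and timely "submission of data at all 6-month, 1-year, and 2-year follow-up visits". The Statistical analysis section fixes the tests. Compliance for the "composite outcome of compliant 6-month, 1-year, AND 2-year follow-up visit will be compared between study arms" with Pearson's chi-squared test, and compliance at each single "follow-up visit will be compared between study arms using Fischer’s exact test". Neither test uses covariates. That section also calls the 6-month, 1-year and 2-year outcomes the primary end-points, but whichever is meant, the stated comparison is unadjusted.

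The only regression model is a secondary one: "generalized estimating equations (GEE) will be used to estimate population-averaged changes in complete and timely follow-up".

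On baseline data, the Data collection section states: "We will collect the name, birth date, donation date, demographic information (gender, race, ethnicity), and contact information for every patient who consents to participate". Age at donation follows from the two dates. Hospital is known because each site enrols its own donors.

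The Sample size calculation section gives 160 per arm and 70% compliance in controls, with 80% power if the intervention rate is 83% and 90% power if it is 85%.

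**The concern.** With a binary outcome and baseline variables held for everyone, an analysis that uses those variables can estimate the same difference in proportions more precisely, provided they predict the outcome. A raw two-by-two test cannot. Chance differences between arms in a prognostic factor then stay in the result as noise.

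The sample size leaves little spare power. It is set to detect a gain of 13 to 15 percentage points, and the lower scenario meets its 80% target only to rounding. A modest gain at no data cost would be useful here. The covariates must be named before outcomes are analysed, because a set chosen afterwards invites selection.

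**Working it through.** **Inputs.** From the Sample size calculation section: n = 160 per arm, p1 = 0.70, p2 = 0.83 or 0.85. The significance level is not stated, so two-sided 5% is assumed. The share of outcome variance explained by the baseline variables (R²) is not given. A range of 0 to 0.10 is assumed.

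**Step 1: reproduce the stated power.** Normal approximation without continuity correction, where d = p2 − p1 and p̄ is the mean of the two rates:

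Power = Φ[(d − 1.96 × SE0) / SE1], with SE0 = √(2p̄(1 − p̄)/n) and SE1 = √([p1(1 − p1) + p2(1 − p2)]/n).

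- 70% v 83%: SE0 = √(2 × 0.765 × 0.235/160) = 0.0474; SE1 = √((0.2100 + 0.1411)/160) = 0.0468; (0.13 − 0.0929)/0.0468 = 0.79; power 78.6%.
- 70% v 85%: SE0 = √(2 × 0.775 × 0.225/160) = 0.0467; SE1 = √((0.2100 + 0.1275)/160) = 0.0459; (0.15 − 0.0915)/0.0459 = 1.27; power 89.9%.

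Exact enumeration of the Pearson test gives 79.1% and 90.3%. The stated 80% and 90% therefore reproduce to rounding. A one-sided 5% level (86.7% and 94.5%) and a continuity-corrected calculation (74.5% and 87.2%) do not match.

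**Step 2: effect of adjustment.** The variance of the marginal risk difference is multiplied by about (1 − R²), so n per arm acts as 160/(1 − R²). Example at R² = 0.05, 70% v 83%: both standard errors shrink by √0.95 = 0.975, giving (0.13 − 1.96 × 0.0462)/0.0457 = 0.86 and power 80.6%.

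| Assumed R² | Effective total N | Power, 70% v 83% | Power, 70% v 85% |
|---|---|---|---|
| 0 | 320 | 78.6% | 89.9% |
| 0.02 | 327 | 79.4% | 90.4% |
| 0.05 | 337 | 80.6% | 91.3% |
| 0.10 | 356 | 82.7% | 92.7% |

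**Step 3: what such an R² would require.** The Discussion says 77% of the cohort is Caucasian. For that one split, with mean compliance 0.765, R² = D² × 0.77 × 0.23/(0.765 × 0.235) = 0.985 × D², where D is the difference in compliance between the two groups. An assumed D of 10, 15 or 20 points gives R² of about 1%, 2% or 4%. An R² of 10% from this split alone would need about 32 points. Several covariates could add up, but the upper end of the range has no support in the document.

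**Step 4: chance imbalance is the same gain, not a second one.** The between-arm difference in a 23% characteristic has standard deviation √(2 × 0.23 × 0.77/160) = 4.7 points. With D = 15 points it adds 0.047 × 0.15 = 0.7 points of noise to a risk difference whose standard error is 4.7 points. As a share of variance that is (0.7/4.7)², about 2%, which is the R² already counted in step 3.

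**Step 5: does adjustment cost anything?** Simulated trials at 70% v 83% compared the standardised risk difference with the Pearson test. With no prognostic value, power was 77.5% adjusted v 78.1% Pearson. At R² of about 3%, 7% and 12% it was 79.4% v 79.0%, 80.8% v 79.4% and 82.8% v 78.8%. Type I error was 5.0% to 5.6% adjusted and 4.7% to 5.7% Pearson. A separate run of 4,000 trials per setting gave 78.4% for both methods at R² = 0, and 82.5% v 78.9% at about 10%. Its simulation error on power is about √(0.784 × 0.216/4000) = 0.65 points, so differences below about one point should not be read closely.

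**Step 6: can the data carry the model?** Expected non-compliant participants: 0.30 × 160 + 0.17 × 160 = 48 + 27 = 75. Five or six terms leave 75/6 = 12.5 to 75/5 = 15 events per term.

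**The case against.** The best defence is that nothing is wrong with the planned test. Pearson's test is valid under 1:1 randomisation and is the test from which the stated power reproduces. Its error rate already allows for chance imbalance, so imbalance adds noise but no bias. All of this stands.

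A reader might infer more than the document supports:

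- **That precision is known to be lost.** The document gives no figure for how well age, gender, race, ethnicity or hospital predicts complete and timely follow-up. If they do not predict it, nothing is lost.
- **That the Background shows these variables are prognostic.** It reports that some trials found "a benefit only in subgroups of patients who were at higher risk for poor adherence at baseline". That concerns mainly where incentives work, which is effect modification. It does not say that the collected demographics predict compliance.
- **That the trial is underpowered as stated.** The gap between 78.6% and 80% is one of approximation. Exact enumeration gives 79.1%.
- **That the GEE should have named covariates.** These are commonly left to a statistical analysis plan, which may exist and is not shown.

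It could also be said that the sponsor declined to pursue power, since the Statistical analysis section says maximising it was not the motive. That sentence explains the choice of policy end-points. A standardised risk difference keeps the end-point and the quantity estimated, and changes only the estimator.

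One practical objection also stands: with 77% of the cohort in one group, some race and ethnicity categories may be small and must be combined by a rule set in advance.

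**Conclusion.** The point holds as an efficiency improvement of uncertain size. The primary comparison is fixed as an unadjusted test, and baseline variables recorded for every participant play no part in it. The planned test is neither invalid nor inconsistent with the sample size.

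At 70% v 83%, adjustment would add about 0 to 2 points of power if R² is at most 5%, and about 4 points at 10% (82.7% v 78.6%). At 70% v 85% the gain at 10% is about 3 points (92.7% v 89.9%). With no prognostic value, power is essentially unchanged. These figures rest on an assumed two-sided 5% level and an assumed R². The lower part of the range is the more plausible one on the scale check in step 3.

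**What to change.** Pre-specify, before outcomes are analysed:

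- **Primary estimate:** the standardised (marginal) difference in the proportion compliant at all three visits, with 95% CI, from a logistic regression of compliance on arm, hospital, age at donation, gender and one race/ethnicity variable collapsed to a few levels fixed in advance, with robust standard errors.
- **Role of the Pearson test:** keep it, unadjusted, as a supportive analysis, and state that the adjusted estimate governs the primary conclusion.
- **Details to settle now:** the race/ethnicity grouping, the form in which age enters, and the handling of any missing baseline entry.

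The cost is a short change of wording and a few lines of Stata. The end-point, data collection and sample size do not change. The sample size statement can stay as it is, since it describes the unadjusted test and needs no assumed R².

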#### Sample size calculation

The total sample size for this study (including participants at both MDJH and MDUM) is *N* = 320. With 160 participants in each arm given the hypothesized follow-up in control group of 70%, we will have 80% power to detect a difference between the study arms if the follow-up rate is 83% in the intervention group, and 90% power to detect a difference between study arms if follow-up in intervention group is 85% (Fig. 2). The hypothesized follow-up in the control group is derived from historical follow-up percentages at MDJH and MDUM.

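### The primary endpoint is a single all-three-visits composite in one section and plural visit endpoints in another, and nothing says which of four planned patient-level tests decides the trial

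*Protocol article*

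**What the plan says.** The protocol article describes the primary outcome in three places.

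- **Abstract, Methods/design:** a single outcome, complete and timely "submission of LKD follow-up data at required 6-month, 1-year, and 2-year time points". It does not say whether all three are needed.
- **Study design:** a single outcome, the rate of complete and timely "submission of data at all 6-month, 1-year, and 2-year follow-up visits". This requires all three. The same section adds: "Outcomes will be assessed separately for each follow-up time point and as a composite outcome over the study period".
- **Statistical analysis:** "Our primary end-points are the living donor policy defined outcomes of complete and timely 6-month, 1-year, and 2-year follow-up". This is plural and lists the visits.

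The Statistical analysis section also sets out the tests. "Rates of patient and center-level compliance for each 6-month, 1-year, and 2-year follow-up visit will be compared between study arms using" introduces Fisher's exact test, one per visit. Pearson's chi-squared test is assigned in the sentence that reads "composite outcome of compliant 6-month, 1-year, AND 2-year follow-up visit will be compared between study arms using". At patient level that makes four comparisons, and none is named as decisive.

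The Sample size calculation section gives one calculation. Its starting point, in per cent, is "With 160 participants in each arm given the hypothesized follow-up in control group of 70". For the smaller of two effects it claims that "we will have 80% power to detect a difference between the study arms if the follow-up rate is 83% in the intervention group". For the larger effect, an intervention rate of 85%, the claimed power is 90%. The section does not say whether the 70% is a rate at one visit or at all three.

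**The concern.** The primary endpoint settles what counts as a positive trial. Under the Study design definition, a benefit at 6 months with no difference in the all-three outcome is a negative result. Under a plural reading of the Statistical analysis section, the same data could be reported as success on a primary endpoint.

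That pattern is foreseeable. The Background notes that incentive effects may fade with time, and the Discussion expects the results to inform center-level and national initiatives. If the choice among the four comparisons were left until the data are in, the false-positive chance could exceed the usual 5%.

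The ambiguity also reaches the sample size. The all-three rate cannot exceed the rate at any single visit, so one 70% control figure is unlikely to describe both endpoints.

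**Working it through.** **1. Reproduce the stated power.** Inputs from the Sample size calculation section: n = 160 per arm, control 0.70, intervention 0.83 or 0.85. The article states no alpha, so two-sided 0.05 is tried. The formula is power = Φ{[d√n − 1.96√(2p̄(1−p̄))] / √(p₁(1−p₁) + p₂(1−p₂))}, where d = p₂ − p₁ and p̄ is the mean of the two rates.

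- 0.70 v 0.83: (0.13 × 12.649 − 1.96 × √0.35955) / √0.3511 = (1.6444 − 1.1753) / 0.5925 = 0.792, so power is 78.6%.
- 0.70 v 0.85: (0.15 × 12.649 − 1.96 × √0.34875) / √0.3375 = (1.8974 − 1.1575) / 0.5809 = 1.274, so power is 89.9%.

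The stated 80% and 90% are reproduced to within two points. Exact power of the Pearson test is 79.1% and 90.3%. Fisher's test gives 74.9% and 87.7%, and a one-sided 0.05 test gives 86.7% and 94.5%; neither fits. The sample size therefore looks like one unadjusted two-sided 5% Pearson-type comparison.

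**2. False-positive chance if any one test suffices.** Four things are assumed because the article does not give them: two-sided 0.05 per test, a claim on any one significant result, a 70% rate at each visit, and the between-visit correlation.

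Bounds under independence:

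- Three tests of exact size 5%: 1 − 0.95³ = 14.3%.
- Fisher's test is conservative here, with actual size 3.8% at 70% and 160 per arm. Three such tests give 1 − (1 − 0.0381)³ = 11.0%.

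Simulation with no effect, 160 per arm, 20,000 trials per row, 70% at each visit, and correlation on a latent normal scale:

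| Latent correlation | Any of 3 Fisher | Any of 3 Fisher or Pearson composite | Composite alone | All-three rate |
|---|---|---|---|---|
| 0 | 11.0% | 14.2% | 5.0% | 34% |
| 0.3 | 10.8% | 13.4% | 4.9% | 42% |
| 0.5 | 10.6% | 12.9% | 4.9% | 47% |
| 0.7 | 10.2% | 12.2% | 5.1% | 53% |
| 0.9 | 8.4% | 10.0% | 5.0% | 60% |

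Visit rates of 80/75/70% or 90/85/80% change little: 8.1–10.6% for the three visits, 9.8–13.3% with the composite, and 4.4–5.1% for the composite alone.

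**3. What the 70% means for the composite.** If 70% is the all-three rate, step 1 is the power of the composite and nothing changes. If it is the rate at each visit, the all-three control rate is 0.70³ = 34.3% under independence, rising to about 60% at the highest correlation tried. Power for the composite then depends on the effect assumed, and it can move either way:

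- The same 13-point gain, 34.3% v 47.3%: (1.6444 − 1.96 × √0.4831) / √0.4746 = 0.41, so power is 66%.
- 83% at every visit with independence, 34.3% v 0.83³ = 57.2%: d = 0.2288 and (2.894 − 1.96 × √0.4965) / √0.4702 = 2.21, so power is 99%.

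The stated 80% and 90% therefore cannot be carried over to the composite without knowing what the 70% is.

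**The case against.** The strongest reply is that the article leans towards the composite. The Study design definition is explicit. The paragraph that uses the plural goes on to offer GEE as a secondary analysis, so that donors who miss one visit can still be counted, and it describes such donors as falling outside the policy. That makes sense only if the policy outcome needs all three visits. The single power calculation, which matches a Pearson test and not a Fisher test, points the same way. On this reading the error rate is 5%.

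This stands as evidence of intent and is a good reason to choose the composite. It does not remove the conflict: the plural wording and the unranked tests remain, and a primary endpoint should not have to be inferred from a remark about GEE.

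A second reply also stands. Multiplicity rules are commonly left to an analysis plan or full protocol, and neither is shown, so the absence of an adjustment is not a finding. The finding is the conflicting definition.

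A reader might go further and infer that every test is run at full alpha and that the trial's false-positive rate is therefore above 5%. The article does not support this. It states no alpha, and nowhere does it say that one significant visit would make the trial positive. Nor does the Background make discordant visits likely; it says only that effects may decline.

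**Conclusion.** The point holds as an inconsistency about which endpoint is primary, and the text of the article alone establishes it. Its possible cost is roughly 8–11% false positives if any of the three visits could carry the claim, and 10–14% if the composite is added, against about 5% for the composite alone. All of this is conditional on the four assumptions in the working. It would be wrong to report 8–14% as the trial's actual error rate, because under the Study design definition that rate is about 5%.

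The sample size section does not say which endpoint its 70% describes. Until it does, the stated power cannot be attached to the composite with confidence.

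**What to change.** - In the Abstract, Study design and Statistical analysis sections, state that complete and timely submission at all three visits is the sole primary endpoint, tested at two-sided 5%.
- Label the three visit-level comparisons secondary and report each with an estimate and 95% confidence interval.
- In the Sample size calculation section, state whether 70% is the all-three control rate. If it is a rate at each visit, give the all-three rate from the historical data at the two hospitals and restate the power for the composite.

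The cost is a few sentences. If 70% is the all-three rate, N = 320 and the stated power are unaffected; if not, the restated power will show whether 320 is still enough. The sponsor gives up claiming success on a single visit.
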